### Aim 3: Impact of operational context, program model, and operating procedures on OPC effectiveness

Our ethno-epidemiological approach will leverage our cohort infrastructure to facilitate ethnographic and qualitative data collection. Data collection will include ethnographic fieldwork in and around OPCs to explore their community and operational contexts (e.g., neighborhood setting, program models), in-depth interviews with PWUD recruited from the study cohort and program staff; and targeted qualitative interview sequences with study cohort participants to examine emerging drug outcomes and service utilization patterns based on analyses undertaken to address Aim 1.

#### Study population, recruitment, and sampling

Qualitative participants will be purposively sampled from the cohort to understand variegated experiences across populations in relation to OPCs. Eligibility criteria for Aim 3 is the same as Aim 1. Program staff participants will include program administrators and frontline staff.

Interviews will be conducted with approximately 150 PWUD and 30 OPC staff across RI and NYC OPCs over the study period. In Year 2, interviews will be conducted with 90 PWUD and 30 OPC staff (n = 30 PWUD and 10 OPC staff per OPC site). PWUD will be recruited from the cohort, while program staff will be recruited during fieldwork. In Years 3 and 4, two targeted interview sequences will be conducted with a total of 60 PWUD (n = 30 PWUD per sequences) across study sites. Targeted interviews will be conducted with participant sub-groups sampled according to criteria used to explain emergent findings and analyses of quantitative data from Aim 1 (e.g., to understand why OPC participants engage in varying levels of substance use treatment).

Interviews will be conducted in English or Spanish and will last approximately 45–60 min. Interviews will be facilitated using sequence-specific topic guides aligned with the aims, and informed by epidemiological and qualitative findings, as well as input from our CAB. Interview guides will be piloted with a small number of participants (n = 5) to assess their suitability (content, flow) prior to implementation and revised to optimize data collection. Interviewers will note key points, notable quotes, and observations about the discussions. Following interviews, ‘member checking’ [78] will occur with participants who will be invited to clarify and amend their interview summary. All participants will receive a $40 honorarium for their time.

#### Ethnographic observation

Approximately 200 h of ethnographic fieldwork will be conducted over the study period. Fieldwork will involve direct observation, unstructured conversations, and engagement with PWUD and staff in and around OPCs. [79, 80] Field notes will be written following each fieldwork session to detail observations and unstructured conversations that occurred. Fieldnotes will aim to situate observations and interactions within each OPC context (e.g., design characteristics), [79, 80] including neighborhood locations and OPC facility characteristics that could influence the implementation and effectiveness of OPC engagement (e.g., security cameras, access to public transit, operating within an SSP). Relevant OPC design characteristics (e.g., injecting booths, security features) will be photographed or diagrammed (with staff permission) to advance analyses of implementation contexts.

#### Analysis

We will integrate and analyze qualitative and epidemiological data drawing on approaches previously used by members of our team. [81–85] Integrating qualitative and ethnographic approaches within the prospective cohort study will add depth to our analyses, [86, 87] thus overcoming challenges associated with self-reported data (e.g., recall of OPC engagement over time, overdose events) through multiple data points and providing a more complete picture of OPC engagement and impacts. Through cross-methodological communication and iterative analysis informed by quantitative data, we will be able to unpack how OPC operational contexts shape access to, and engagement with, these interventions and impacts on participant-level outcomes.

Transcripts and field notes will be imported into Dedoose, a qualitative data management and analysis software, and organized by interview series. Data will be coded using deductive and inductive approaches involving the use of a priori categories (deductive) and emergent categories (inductive) through line-by-line coding, [88] and constant comparative analysis. [89] This will be operationalized by developing coding frameworks comprised of categories from the interview guides, and expanded to include emic categories specific to OPCs, the implementation or community contexts, and participant groups based on social identities. Data will be subjected to a process whereby we assign data segments to these categories, summarize the content of each category, and examine contradictory evidence. The coding framework will be further updated through iterative analysis informed by other data sources (Aims 1–2), which will primarily involve the use of emerging cohort-based analyses and neighborhood-level data (Aim 2) to refine coding categories. In summary, grounded hypotheses developed from qualitative analyses will generate insights into, for example, how operational contexts (e.g., hours of operation, facility location and design) produce differential outcomes across diverse sub-groups of PWUD.

### Aim 4: Operational OPC costs and potential cost savings to the health and criminal justice systems

We will estimate operational costs of implementing OPCs in RI and NYC that will inform future implementation in other jurisdictions. Collecting and comparing healthcare and criminal justice system utilization between OPC and non-OPC participants will generate cost-saving/offset estimates from using the OPC. These data will inform future cost-effectiveness analysis that incorporates long-term health and cost outcomes.

#### Determine start-up and ongoing costs of OPCs

We will use established micro-costing methods to estimate the operational costs of OPC study sites in RI and NYC. [90, 91] One-time start-up costs (e.g., staff training, equipment purchases), ongoing variable costs (e.g., staff labor time for each service delivered), ongoing time-dependent costs (e.g., regular staff meetings, record-keeping), and overhead costs will be calculated from the budgetary perspective of the study sites. Cost calculations will use resource costing methods which are computed by multiplying the price weight for each resource unit by the respective units of service and then summing the values across all services. [92, 93] Labor costs will be valued using local wage rates for comparable OPC staff positions from the Bureau of Labor Statistics as well as national wage rates for sensitivity analysis.

We will use site records on services provided to OPC clients, estimates of the time required to provide services obtained through staff interviews at each site, and site financial records to conduct cost analyses. We will adapt the Drug Abuse Treatment Cost Analysis Program (DATCAP) instrument to conduct data collection. [94] Results will be reported as annual costs for each of the sites and as a total average for each location (RI and NYC). For each total cost result reported, each cost component will be reported (i.e., start-up, ongoing (i.e., variable and time-dependent costs), and overhead costs). We will also report total costs per client served and per overdose reversed.

#### Calculate additional costs and cost savings to the healthcare and criminal justice systems for OPC study participants compared to non-OPC SSP study participants

To determine additional healthcare and criminal justice system savings and costs from OPC use, we will use self-reported data from Aim 1 on use of medical, social, and substance use treatment services and engagement with the criminal justice system. These data will be collected from participants in the baseline and follow-up assessments using questions from NIDA’s Seek, Test, Treat, and Retain Service Utilization Domain that details medical service utilization. [95] Self-reported data on health care encounters has been used extensively in previous research. [96, 97] Health-related quality of life measures will also be collected using the PROPr instrument to inform future cost-effectiveness analysis. [98] We will use various established sources for health care payment estimates and criminal justice costs to estimate healthcare system and criminal justice system costs. [99–102] 

Costs based on health services and criminal justice utilization will be compared between OPC and non-OPC SSP participants 6, 12, and 18 months after baseline to estimate incremental costs per participant and potential downstream cost offsets/savings resulting from OPC use. A health care system and criminal justice system cost (societal) perspective will be taken in this economic analysis. Analyses will be conducted using a generalized linear mixed model (GLMM), which allows for the inclusion of random effects and is recommended for economic analyses. [93] The method of recycled predictions will be used to obtain the final predicted mean cost values, which will be summed and tested. [93] To account for sampling uncertainty in point estimates, the *p*-values and standard errors will be estimated using nonparametric bootstrapping techniques. For the 18-month comparison, 3% discounting will be applied. [92] Using these methods, we will estimate the predicted mean value by resource, study group (e.g., OPC and non-OPC SSP) time period (6, 12, and 18 months), and geography (RI, NYC). TThe net value of OPCs will then be calculated by taking the difference between the average estimated total cost of OPCs and non-OPC SSPs to determine if the OPCs have a greater net benefit compared to non-OPCs.

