#### Outcomes measured through administrative health records

To provide a comprehensive assessment of change in health conditions associated with OPC use, we complement self-reports with administrative health records. Participant identifiers will link participants to their administrative health records. Table 2 presents the sources and types of information we plan to collect, leveraging our partnerships with the NYC Department of Health and Mental Hygiene (DOHMH), NYS Office of Addiction Services and Supports (OASAS), the RI Department of Behavioral Health, Developmental Disabilities, and Hospitals (BHDDH), and the Rhode Island Department of Health (RIDOH). We link participants to their health records 18 months prior to their first survey date and for up to three years post-enrollment, to track pre- and post-OPC changes in their health using probabilistic matching with the last four digits of each participants’ social security number, first and last name, date of birth, and sex. [42] We use a minimum, common set of data sources, including Medical Examiner, Medicaid, and data from licensed substance use disorder treatment facilities (through OASAS and BHDDH), ensuring a high degree of comparability across jurisdictions. In Rhode Island, we can also link participants to prescription drug monitoring program data, as we have done in prior work. [43]

**Table 2 Tab2:** Administrative health record data sources linked with study participants

Domain	Items	NYC data^1^	Rhode Island data^2^
Fatal overdose	All drug overdose, stimulant, and opioid	Office of Chief Medical Examiner	Office of Chief Medical Examiner
Non-fatal overdose	All drug overdose, stimulant, and opioid	NYC Regional Health Information Exchange (RHIO), Statewide Planning and Research Cooperative System (SPARCS),^3^ Medicaid	Emergency medical services data, Medicaid^4^
Drug-related health conditions	Hepatitis C, HIV, skin and soft-tissue infections, infective endocarditis	NYC RHIO, SPARCS, and Medicaid	Medicaid^4^
Emergency department visits	Overall ED use, drug-related emergency department (ED) visits	NYC RHIO, SPARCS, and Medicaid	Medicaid^4^
Substance use disorder treatment	Initiation in a licensed treatment program, including medications for OUD	OASAS and Medicaid	Prescription drug monitoring program, BHDDH, and Medicaid

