SAFER offers four methodological and substantive contributions. First, the study relies on a highly rigorous and novel study design. Most previous individual-level evaluations focus on clients attending the OPC, [15] but do not contrast findings to those in an unexposed comparison group, limiting causal inference. To address this limitation, as part of Aim 1, we will recruit from two types of venues: 1) directly from OPCs and 2) SSPs that do not intend to operate an OPC. This design enables both within- and between-person analyses of OPC use over time and provides a comparison group of participants who are engaged with harm reduction services but are not exposed to an OPC. Further, we leverage a combination of regular survey assessments and linked administrative health records to improve our ability to capture key outcomes such as overdose, drug-use related health problems, and connection to services, while overcoming biases associated with self-report and loss to follow-up. [109] Second, we leverage novel analytic approaches to overcome the limitations of previous research. For example, substance use, overdose, and engagement in treatment are interconnected, often recurrent events. We investigate the effect of OPC use on these outcomes using an innovative, multi-state, marginal structural Cox modeling approach. [45, 46] In Aim 2, we adopt a novel causal inference approach to address concerns of structural confounding given differences between neighborhoods that do and do not decide to open an OPC service. Third, we have an unprecedented opportunity to gain qualitative insights into the types and elements of program models most effective at improving public health and community outcomes. These have not been comparatively studied across sites in any country. [13] In Aim 3, we will be able to use rigorous qualitative methods to assess how the type of model implemented (e.g., medical vs. peer-supervised), location (i.e., co-located within an SSP, mobile services, or as an extension service to an opioid treatment program), wraparound services provided, and geographic context shape outcomes associated with OPC use. Fourth, work conducted to test Aim 4 will be the first to estimate the range of costs of different operating OPCs in the US as well as the economic value of OPCs that may guide future implementation and policy in other areas of the country.

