While our proposed study has the potential to make lasting contributions to our understanding of the impact of OPCs on the health of PWUD and local communities, it also poses some limitations. First, the political and ethical constraints on randomization limit causal inference. However, we propose several approaches to address time-dependent confounding in Aim 1, and the lack of a counterfactual comparison neighborhood in Aim 2. Second, the limited number of OPCs we evaluate (up to three OPCs across the two jurisdictions) limits our ability to make quantitative inferences about the impact of different models of OPC service delivery. However, we will explore this in our qualitative analysis (Aim 3), with the intent of quantifying differences in outcomes across service models in future research across a wider spectrum of OPCs. Third, loss to follow-up may constrain our ability to evaluate long-term outcomes associated with OPC use. However, our experience with longitudinal follow-up of similar populations, an extensive plan for cohort retention, and plans to complement survey data with administrative data, reduce this concern.

Our study leverages a multi-site design to provide generalizable insights about the effectiveness of OPCs. We will consider the extent to which the effectiveness of OPCs varies by the type of jurisdiction (NYC, RI), and will generate insights about the types of operational contexts, program models, and operating procedures which contribute to the most promising outcomes. Finally, we will collect rich data on the costs and savings associated with the implementation of OPCs. Policymakers and practitioners considering opening OPCs in other jurisdictions will be able to use our findings as an evidence base to inform the types of approaches that could work best in their own context.

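### Aim 4 costs health care and treatment use from self-report interviews alone, leaving unused the linked records that could show use before death or after loss to follow-up

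*Protocol article*

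**What the plan says.** The Aim 4 section on additional costs and savings names the source of utilisation: "we will use self-reported data from Aim 1 on use of medical, social, and substance use treatment services", together with criminal justice engagement. It adds that "These data will be collected from participants in the baseline and follow-up assessments". The support offered for this choice is precedent: "Self-reported data on health care encounters has been used extensively in previous research". Outside sources enter as prices, not as counts of use: "We will use various established sources for health care payment estimates and criminal justice costs". The resulting costs "will be compared between OPC and non-OPC SSP participants 6, 12, and 18 months after baseline", using a generalized linear mixed model (GLMM), recycled predictions and a bootstrap for sampling uncertainty.

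The Aim 1 section on administrative health records says of the same people: "We link participants to their health records 18 months prior to their first survey date and for up to three years post-enrollment". Table 2 lists emergency department visits and substance use disorder treatment among the linked items. The Aim 1 analysis section measures its outcomes from both records and surveys, and adds inverse probability of censoring weights for the Cox models.

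The Discussion credits the combination of surveys and records with "overcoming biases associated with self-report and loss to follow-up". On loss to follow-up it says that retention experience, a retention plan and "plans to complement survey data with administrative data, reduce this concern".

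**The concern.** Someone who dies or is lost gives no further interview, so emergency, hospital and treatment use after the last completed interview cannot be self-reported. For an overdose death this includes any care for the fatal event, which is a cost that an OPC might be expected to avert. The monthly check-ins do not fill the gap: as described, they cover contact details, OPC use and overdose counts, not service use.

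Loss in this population is plausibly related to cost, and the study itself hypothesises that OPC use changes fatal overdose and service engagement. If loss differs by group, the cost contrast can be biased in either direction. Aim 4 uses that contrast to judge whether OPCs bring a net benefit, and the Discussion offers it as a guide for policy. Emergency department use would also be measured from records plus surveys in Aim 1 but costed from surveys alone in Aim 4, so the two aims could disagree about the same people.

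**Working it through.** **What each part of the article covers**

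| Item | Aim 1 outcomes | Aim 4 costs |
|---|---|---|
| Source of emergency and treatment use | Surveys and linked records | Surveys |
| Named step for loss | Censoring weights (Cox models) | None named |
| Window | Records from 18 months before to 3 years after enrolment | Months 6, 12, 18 |

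The record window spans the whole 18-month cost window. Interviews are at baseline and months 6, 12 and 18, and Table 1 gives a 6-month recall for emergency visits, hospital nights and treatment. A missed interview therefore leaves about six months of use unobserved, and a death leaves the time since the last interview unobserved.

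**Illustration of size**

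The article states no attrition rate, cost ratio or cost figure, so there is nothing to reproduce and the values below are assumptions. Let L be the share unobserved, r the cost of those unobserved relative to those observed, and 1 the observed mean. Then:

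- true arm mean = 1 − L + L·r
- understatement of an arm mean = 1 − 1/(1 − L + L·r)

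| L | r = 1 | r = 1.5 | r = 2 | r = 3 |
|---|---|---|---|---|
| 10% | 0% | 4.8% | 9.1% | 16.7% |
| 20% | 0% | 9.1% | 16.7% | 28.6% |
| 30% | 0% | 13.0% | 23.1% | 37.5% |

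For the contrast, assume L = 20% (OPC) and 30% (SSP), with no difference among those observed:

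- r = 1.5: 1.10 v 1.15; (1.10 − 1.15)/1.15 = −4.3%
- r = 2: 1.20 v 1.30; (1.20 − 1.30)/1.30 = −7.7%
- r = 3: 1.40 v 1.60; (1.40 − 1.60)/1.60 = −12.5%

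Swapping the two loss rates reverses the sign. Equal loss with the same r in both arms, or r = 1, gives a missed difference of zero. These figures describe an unadjusted comparison of observed means. The planned GLMM would remove part of the bias to the extent that earlier observed costs predict the loss.

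**How much the records could recover**

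A Table 2 footnote puts Medicaid coverage of the target population at 88% in RI and 75% in NYC. If coverage among those lost is the same and matching succeeds, an unobserved 20% falls to 0.20 × 0.12 = 2.4% in RI and 0.20 × 0.25 = 5% in NYC. NYC could do better, because SPARCS is described there as all-payer.

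**The case against.** The strongest reply has four parts.

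**The model is not a completer average.** A GLMM with random effects keeps the 6- and 12-month data of someone lost by month 18, and its estimates are valid if loss is missing at random given the model. That stands, and the illustration above should not be read as the bias of the planned model. But the model observes nothing after the last interview, missing at random is doubtful when the reason for loss may be overdose or worsening health, and recycled predictions could assign a survivor's costs to someone who died. The bootstrap does not address selection.

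**A reader might infer that the article contradicts itself, or that all use by jailed participants is lost.** Neither is supported. The Discussion ties the records to key Aim 1 outcomes, says the concern about loss is reduced rather than removed, and nowhere promises records for costing. No passage says that people in jail are not interviewed, and someone seen after release can report by 6-month recall. Nor does a death remove later costs, since none arise; what is lost is use before it. It would also be too strong to say that all the records are in hand: only the RI data are described as already available.

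**Missing-data handling belongs in the fuller plan.** That is fair for weighting or imputation, and their absence here is not the point. The data source, however, is stated, and that choice is what is questioned. The article does not rule out a records-based analysis, so adding one is consistent with it.

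**Filling gaps from records has its own bias.** If loss differs by group, using records only for missed intervals makes the measurement source differ by group. This objection is correct and shapes the fix. Table 2 also does not list hospital nights or social services, so records cannot replace the survey for every cost item. Self-report does have the merit of one instrument across both jurisdictions.

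**Conclusion.** The point holds as a design weakness that should be fixed. Aim 4 names self-report interviews as its one source of health care and treatment use, while linked records on the same participants, spanning the whole cost window, are planned and relied on elsewhere for the same problem. The remedy is unused; the article does not contradict itself.

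The size of the bias cannot be derived from the documents. It is zero if those lost cost the same as those retained. The 4% to 13% of the SSP mean rests on assumed loss of 20% v 30%, cost ratios of 1.5 to 3, no difference among those observed and no model adjustment. The conclusion itself rests on loss and death being plausibly related to cost beyond what earlier waves reveal.

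**What to change.** Keep the self-report analysis. Add a prespecified analysis that takes emergency department visits and substance use disorder treatment from linked records for all participants in both groups, up to month 18 or the date of death, with zero cost after death. Include inpatient stays where the linked Medicaid or SPARCS data supply them. Using one source for everyone avoids a measurement difference between groups.

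Report agreement between the two sources among participants who completed the surveys. Use records to fill missed survey intervals only as a further sensitivity analysis.

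The cost is extra programming and confirmation that the data use agreements cover costing; no new participant contact is needed. Coverage stays incomplete: RI emergency department visit data are Medicaid only (88% of the target population), and Medicaid reaches 75% in NYC, though SPARCS is all-payer there. Social service and criminal justice costs are not corrected, because Table 2 links no records for them.

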### Measurements

#### Survey instrument (conducted at baseline, 6, 12, and 18 months)

The instrument incorporates common measures developed by the NIDA Harm Reduction Research Network, (37) measures from a prior data harmonization effort for OPC measures, [37] and previous work conducted by the study team. [38–41] In addition, the instrument underwent multiple rounds of review and cognitive testing by our partners at the OPCs and SSP partner organizations, including service staff and participants. A summary of our measures is provided in Table 1 and our baseline instrument is included in the Appendix. Participants receive $40 for each completed baseline and follow-up survey.

**Table 1 Tab1:** Domains and corresponding items measured in baseline and follow-up surveys given to study participants

Domain	Items
*Primary Exposures*	
OPC use	In the past 30 days: used an OPC, name of OPCs used, frequency of use, proportion of drug use consumed at OPC
*Primary Outcomes*	
Overdose	Lifetime and past 30-day nonfatal overdose
Hepatitis C	Lifetime and past 6-month hepatitis C test result, past 6-month positive hepatitis C diagnosis, receipt of treatment
HIV	Lifetime and past 6-month HIV test result, past 6-month positive HIV diagnosis, receipt of ARV and PrEP
Other infections	Past 6-month skin and soft tissue infections, mode of treatment for infection, past 6-month diagnosis of endocarditis
Healthcare use	Past 6-month: number of times used the emergency room to access health care; number of nights spent in the hospital
Harm reduction service use	Year and month of first use; type of services used and frequency of use in the past 3 months
Substance use disorder treatment	Past 6-month: referral to treatment; source of referral; enrollment in treatment; current status of enrollment
*Confounders*	
Drug use	Lifetime, past 30 day, and past 7 day self-reported by type of drug and mode of use
Injection practices	Past 30 days and past 7-day injection practices
Reasons for using OPC	No safe place to use, prior overdose, change in drug dealer, concern about safety of the supply
Syringe disposal	In the past 30 days, number of days: disposed of syringes in a public place; in a hazardous waste container
Demographics	Age, sex, gender identity, race and ethnicity, education
Socioeconomic status	Housing status, zip code, employment, income, money in exchange for sexual activities

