#### Analyses

We use a custom instance of REDCap™ to conduct field-based surveys, which allows for direct transfer and storage of data into our institutions’ secure, HIPAA-compliant, secure computing environments.

To evaluate the effectiveness of attending OPCs on outcomes, we will conduct time-to-event and multi-state analyses. [44] Our primary outcomes will include fatal and non-fatal overdoses, injection-related infections (i.e., skin and soft tissue infections, endocarditis), emergency department use, and substance use disorder treatment initiation. We will measure these outcomes using administrative health records and survey data. Our time-updated exposures of interest will be any use of an OPC in the past month, as well as two measures of exposure “dose”: intensity of use (e.g., daily vs. non-daily) and the fraction of drug use conducted at an OPC in the past month (examined as continuous and > 50% vs. lower). All participants will be asked about OPC use regardless of recruitment source, which will permit analyses of time-varying exposures (e.g., persons recruited from an SSP with no OPC may use an OPC located at another site, which will be captured in our data).

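### Aim 4 draws a net-benefit conclusion from a cost difference alone and calls a two-sector cost perspective societal; the planned calculation supports only a statement of net cost or savings

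*Protocol article*

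**What the plan says.** All of the disputed text is in one place, the Aim 4 subsection on additional costs and cost savings for OPC compared with non-OPC SSP participants.

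- **Perspective:** "A health care system and criminal justice system cost (societal) perspective will be taken in this economic analysis".
- **What is compared:** "Costs based on health services and criminal justice utilization will be compared between OPC and non-OPC SSP participants 6, 12, and 18 months after baseline".
- **How the net value is formed:** it is "calculated by taking the difference between the average estimated total cost of OPCs and non-OPC SSPs".
- **What is concluded from it:** the difference is used "to determine if the OPCs have a greater net benefit compared to non-OPCs".
- **Where health goes:** "Health-related quality of life measures will also be collected using the PROPr instrument to inform future cost-effectiveness analysis".

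The opening of Aim 4 describes the aim as producing cost-saving or offset estimates and defers the rest: "These data will inform future cost-effectiveness analysis that incorporates long-term health and cost outcomes". The list of aims in the Introduction also limits Aim 4 to OPC costs and potential savings in the two systems. The Discussion nevertheless presents Aim 4 as giving the economic value of OPCs, as a possible guide to policy elsewhere.

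**The concern.** The conclusion is broader than the quantity it is drawn from. OPCs exist to prevent overdose harm, so a judgement of net benefit has to weigh health against cost. The stated calculation has only a cost input. If OPC participants do better but cost more, the cost difference is positive and the stated comparison returns no greater net benefit, however large the health gain. If they do worse but cost less, it returns a benefit.

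The perspective label adds to this. Two sectors are named, and sources of unit costs are described only for those two. The label tells a reader that wider consequences have been counted. Employment and income, for example, are recorded (Table 1: "Housing status, zip code, employment, income"), but they are listed among the confounders and no costing of them is described.

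What is at stake is the wording of the Aim 4 conclusion, which the Discussion addresses to policymakers. The Aim 1 and Aim 2 analyses are not affected.

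**Working it through.** The document gives no economic figure for Aim 4: no expected cost difference, health gain or value per unit of health. There is nothing to reproduce, so the check sets the statements side by side and then tests the logic.

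**1. What the rule can show.** Let dC be mean total cost with OPC minus mean total cost with non-OPC SSP. The stated net value depends on dC alone. A net benefit that values health has the form NMB = λ × dQ − dC, where dQ is the difference in quality-adjusted life-years (QALYs) and λ is the value per QALY. The two agree in general only if dQ = 0. This holds whichever cost components enter the total.

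**2. Does the plan assume dQ = 0?** No. The Aim 1 analysis section states: "Our primary outcomes will include fatal and non-fatal overdoses, injection-related infections". It goes on to hypothesise a lower hazard of overdose with OPC use. The plan expects health to differ, so equal health effects cannot be the unstated ground for a cost-only conclusion.

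**3. Does health enter the Aim 4 comparison elsewhere?** Quality of life is collected but reserved for later work. The subsection on start-up and ongoing costs reports cost per overdose reversed, but only as a description of the OPC sites. It does not feed the comparison with SSPs.

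**4. Illustration of direction only; every input is assumed.** Take dC = +$500 per participant. The cost-only quantity is −$500 whatever happens to health. The break-even health gain is dQ = dC / λ:

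| λ per QALY | break-even dQ | NMB at dQ = 0.02 |
|---|---|---|
| $50,000 | 500 / 50,000 = 0.010 | 1,000 − 500 = +$500 |
| $100,000 | 500 / 100,000 = 0.005 | 2,000 − 500 = +$1,500 |
| $150,000 | 500 / 150,000 = 0.0033 | 3,000 − 500 = +$2,500 |

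Below break-even the two quantities have the same sign; above it they have opposite signs.

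**5. Survival can itself raise cost.** Assume the same monthly cost c while alive in both groups, deaths spread evenly over 18 months, and 18-month mortality of 2% against 4%. Mean cost is c × 18 × (1 − m/2), so the lower-mortality group costs c × 18 × (0.04 − 0.02)/2 = 0.18c more. For c = $500, $1,000 and $2,000 that is $90, $180 and $360 per person. Under these assumptions a cost-only rule counts averted deaths against the OPC.

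Steps 4 and 5 show that the conclusion can point the wrong way. They do not estimate how likely or how large that is in this study.

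**The case against.** The strongest reply is that Aim 4 is openly a cost and cost-offset analysis. The list of aims, the opening of Aim 4 and the subsection heading all say so, and cost-effectiveness is expressly deferred. The sentence at issue defines net value as a cost difference, so net benefit could be read as net cost benefit, and as a net cost the sign would be correct. Overdose outcomes are tested separately in Aim 1, so a reader would see both results. The two sectors are named just before the societal label.

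Much of this stands, and it rules out several stronger readings that a reader might infer:

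- **That omitting QALYs is an error.** It is a disclosed design choice. An 18-month QALY analysis would also cut off most of the survival gain from an averted death, which is a fair reason to wait for a longer-term analysis.
- **That the plan ranks OPCs on a stated adoption rule.** It gives no threshold, and the direction (lower cost means greater benefit) is implied, not written.
- **That a dollar amount of benefit is left out.** Any such figure rests wholly on assumed inputs.
- **That social services and property values are wrongly left uncosted.** Self-reported social service use is named as an input to the cost work, so whether it is costed is unclear. Property values are neighborhood-level Aim 2 outcomes and do not belong in a participant-level cost model.

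The disclosed scope does not rescue the final step. It shows that the conclusion exceeds the analysis: the aim is limited to cost offsets, yet the subsection ends by determining net benefit. Reading the term as net cost is possible, but the text does not say so, and the ordinary meaning of the term includes health.

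**Conclusion.** The point holds as a mismatch between calculation and conclusion. The planned quantity is a net cost across two sectors. With health effects excluded and cost-effectiveness deferred, it cannot support a net-benefit determination, and health care plus criminal justice is not a societal perspective. Taken as written, an OPC that improves health at added cost would be reported as having no greater net benefit.

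The size cannot be derived from the document. The finding rests on the stated text and on one inference: that a lower total cost is what would be read as greater net benefit, since a cost-only difference offers no other reading. It does not depend on the illustrative figures. No estimator, model or data item is wrong on this account. What needs correcting is what Aim 4 may conclude.

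**What to change.** In the Aim 4 subsection on additional costs and cost savings:

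1. Rename the result as net health care and criminal justice cost (cost offset or savings).
2. Describe the perspective as a two-sector one and delete the societal label.
3. Delete the net-benefit determination, and state that net benefit is left to the planned future cost-effectiveness analysis that includes health outcomes.
4. Carry the same wording into the Discussion where it refers to economic value.

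This changes wording only; data collection, the mixed model and the bootstrap stay as planned. It costs Aim 4 the claim of net benefit, which the calculation does not support. An 18-month QALY or net monetary benefit analysis would be an optional addition with the truncation drawback noted above, and this point does not ask for it.
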